#### Primary aim 2: implementation strategy

##### Reach

We define *reach* metrics as the proportion of target population that gained access to the ICBHSS initiative services using the annual community household surveys. We will assess the implementation strategy through individual-level ICBHSS participation with community-level (vis-à-vis CHWs) and facility-level health service utilization using health service coverage estimates and early service access for child health. We will use a mixed-effects generalized linear model to compare pre-intervention to post-intervention proportions for each *reach* metric while adjusting for clustering at the facility and district level and time and allowing for district-level estimates to be random effects. Our primary analysis will not include adjustment for individual-level characteristics, as each district will serve as its own control.

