Following this successful preliminary pilot phase and considering the need, IH was requested by the MoH to expand the ICBHSS model to additional sites starting in 2018. In collaboration with the MoH and technical partners, IH is replicating the ICBHSS model in 21 distinct rural health facilities in four additional districts. In collaboration with MoH partners, IH’s ICBHSS program team designed an implementation strategy for this expansion to enhance adoption, implementation, and sustainability of the model [34–36]. This strategy enables a rollout to a new district every 12 months, and is based on pilot experience, local contextual factors as well as budgetary and feasibility considerations. As part of this expansion launched in 2018, IH and MoH partners designed a stepped-wedge randomized trial to enable a rigorous assessment of intervention effectiveness and implementation strategies to inform national policy.

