Given the baseline population need, preliminary effectiveness results, and MoH request for scale-up, we deem it unethical to withhold the intervention from any of the comparison sites. Logistical and financial constraints to launch the ICBHSS model already require the sequential implementation needed for a stepped-wedge trial. This protocol is the best fit considering the limitations from the initial pilot using a single-arm, repeated cross-sectional design and the need for generalizable findings to support translating results into practice [45, 46]. Annual data collection, while an increased demand of resources and cost, was deemed both feasible and beneficial, as it will allow regular quantitative and qualitative data analysis and iterative dissemination of results, internally to support programmatic improvements, and with MoH partners for embedded research practices [47]. Our objective in this paper is to describe the research protocol of this pragmatic hybrid effectiveness-implementation study to measure the effectiveness and implementation strategy of the ICBHSS initiative over 48 months in rural northern Togo using an adapted RE-AIM framework.

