#### Stepped-wedge cluster randomized control trial

This pragmatic design leverages the sequential or staggered rollout of the ICBHSS model and will facilitate an assessment of effectiveness as well as implementation strategy through coverage and adoption metrics by comparing geographically organized clusters [50, 51]. It includes four clusters that organize intervention health facilities by district: Bassar, Binah, Dankpen, and Kéran. The ICBHSS cluster initiation order will be randomized annually with four steps, as it was independently determined by the IH programs team that baseline health needs were similar in each cluster. Community-based household surveys adapted from Demographic and Health Survey (DHS) modules previously implemented in Togo [3] and focusing on demographic, maternal, and child health data will be conducted in each cluster at baseline, 12, 24, 36, and 48 months.

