##### Adoption

We define *adoption* metrics for this study as the proportion of the community and providers changing health-seeking or providing behavior. Our evaluation of *adoption* will be completed using routine programmatic data and annual community household surveys. Through this domain, we will assess implementation strategy measures using community-level engagement and behavior change by the individual-level uptake of the ICBHSS intervention. We will test whether these proportions increased, applying the same approach described in the *reach* evaluation measures through mixed-effects generalized linear models.

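### Reach and adoption: the single pre/post term is unbiased only if the effect is the same at 1, 2, 3 and 4 years of exposure, and two-year recall breaks this for the maternal outcomes

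*Protocol article*

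**What the plan says.** **Layout.** The stepped-wedge section of the protocol article says of the trial: "It includes four clusters that organize intervention health facilities by district: Bassar, Binah, Dankpen, and Kéran". It adds: "The ICBHSS cluster initiation order will be randomized annually with four steps". On timing, the context section states: "This strategy enables a rollout to a new district every 12 months". Household surveys "will be conducted in each cluster at baseline, 12, 24, 36, and 48 months".

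**Model.** The Reach section says: "We will use a mixed-effects generalized linear model to compare pre-intervention to post-intervention proportions for each" reach metric, "adjusting for clustering at the facility and district level and time and allowing for district-level estimates to be random effects". The Adoption section tests for an increase by "applying the same approach described in the" Reach section, and Table 4 names mixed-effects generalized linear models for the child-care and maternal care cascades. No term for time since rollout is mentioned.

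**Recall windows.** In Table 4 the reach indicators for prenatal care, facility birth, home birth and post-natal care all look back two years. CHW visits, CHW treatment and facility care look back one year.

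**The concern.** With one district starting each year and all districts surveyed yearly, the post-rollout data mix one to four years of exposure. A single pre/post term treats them as one effect. If the measured effect differs by year of exposure, the estimate is a weighted sum of the yearly effects, and the weights are set by the layout and the correlation rather than by any question the trial asks. Adjusting for time and district does not remove this; the district adjustment is what makes the late weights negative.

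Reach and adoption carry the second primary aim and are meant to inform national policy. A programme whose coverage grows could be reported as having little effect, and one that fades could be reported as better than its average. For the two-year-recall outcomes the measured effect differs by year by construction, even if the programme works at full strength from its first day.

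**Working it through.** The protocol gives no figure for the reach or adoption models, so there is none to reproduce. The check finds what the single term estimates in the stated layout.

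**Inputs from the protocol.** Four districts, four steps 12 months apart, surveys at 0, 12, 24, 36 and 48 months. If the first district starts just after baseline, exposure at survey is 1 year in four district-surveys, 2 years in three, 3 years in two and 4 years in one.

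**Assumptions.** Linear scale (an approximation to the generalized linear model), equal district sizes, categorical survey period and a random district intercept. Let r be the correlation between two survey means of the same district. With the ICC of 0.005 (given for mortality, borrowed here) and 7600 × 0.8 / (4 × 5) = 304 women per district-survey (taking 7600 as the total over all surveys, which is not stated):

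r = 0.005 × 304 / (1 + 303 × 0.005) = 1.52 / 2.515 = 0.60.

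If 7600 is per survey, there are 7600 × 0.8 / 4 = 1520 women and r = 7.6 / 8.595 = 0.88.

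**Weights.** Take the post-rollout indicator. Subtract its survey mean (0, 0.25, 0.5, 0.75, 1), then subtract λ times the district's deviation from the overall mean (0.3, 0.1, -0.1, -0.3), where λ = 5r / (1 + 4r). Summing over exposed cells by year of exposure gives:

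- year 1: 1.5
- year 2: 0.75 - 0.3λ
- year 3: 0.25 - 0.4λ
- year 4: -0.3λ

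Each is divided by their total, 2.5 - λ.

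| r | λ | Year 1 | Year 2 | Year 3 | Year 4 |
|---|---|---|---|---|---|
| 0 | 0 | 0.60 | 0.30 | 0.10 | 0.00 |
| 0.40 | 0.769 | 0.87 | 0.30 | -0.03 | -0.13 |
| 0.60 | 0.884 | 0.93 | 0.30 | -0.06 | -0.16 |
| district fixed effects | 1 | 1.00 | 0.30 | -0.10 | -0.20 |

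Year 4 has negative weight for any r above 0. Year 3 has negative weight once λ exceeds 0.625, that is, r above 0.25.

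**Expected estimates.** The effect profiles are assumptions. At r = 0.60 the linear rise gives 10 × 0.93 + 20 × 0.30 - 30 × 0.06 - 40 × 0.16 = 7 after rounding (6.8 with unrounded weights).

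| Measured effect, years 1/2/3/4 | Mean | r = 0 | r = 0.40 | r = 0.60 | Fixed effects |
|---|---|---|---|---|---|
| 10/20/30/40 points | 25 | 15 | 8.3 | 6.8 | 5 |
| 30/20/10/0 points | 15 | 25 | 31.7 | 33.2 | 35 |
| 0.7/0.9/1/1 (fast uptake) | 0.90 | 0.79 | 0.71 | 0.69 | 0.67 |
| 1/1/1/1 | 1 | 1 | 1 | 1 | 1 |
| 0.5/1/1/1 (two-year recall, true effect 1) | 0.875 | 0.70 | 0.57 | 0.54 | 0.50 |

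The last row follows from the recall window. Twelve months after rollout, about half of a two-year window lies before it, so an immediate constant effect is measured at about half its size in year 1 and in full afterwards. Year 1 carries most of the weight, so the estimate falls to about half.

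**Sensitivity.** With 5/7/4/5 facilities per district (counted from Table 3), facility and district random effects in several combinations, and all 24 rollout orders, the linear rise returns 0.125 to 0.241 of its four-year value, or 5.0 to 9.6 of 40 points. Adding random district treatment effects gives 0.128 to 0.153.

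**Alternative model.** With one indicator per year since rollout, the yearly effects are estimable and the linear profile is recovered exactly. Relative to the single term, the standard error of the year 1 to 3 mean is 1.21 times at r = 0.40, 1.28 at r = 0.60 and 1.37 with fixed effects. At r = 0.60 the ratio is 1.83 for year 3 alone and 2.48 for year 4.

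**The case against.** The strongest reply is that the bias needs an effect that changes with exposure, and the protocol gives reasons to expect early uptake: an eight-month planning stage before each start, training before service begins, and fee removal as a policy. The first exposed survey comes after a full year, and the indicators with one-year recall could be near plateau by then. This stands. With fast uptake the loss is about a quarter (0.69 against 0.90), and with a constant effect there is none. It does not help the two-year-recall outcomes.

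A second reply is that the sentence is condensed and the coding may be settled in an analysis plan. That is possible, but the article does state the comparison as pre against post and lists the adjustments, and exposure time is not among them.

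A third is that r is assumed: the sample total is ambiguous, the ICC was given for mortality, and at r = 0 no weight is negative. This is correct, and the range is shown for that reason. Even at r = 0 the four-year effect has no weight.

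Four stronger readings are tempting but not supported:

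- *A growing effect is always estimated below every yearly effect.* Not so: 0/30/30/30 gives about 2 at r = 0.60, above its year 1 effect of 0.
- *The trial fails to estimate a 48-month effect.* The stated aim, "to measure the effectiveness and implementation strategy of the ICBHSS initiative over 48 months in rural northern Togo", gives the duration of the study; no effect after 48 months of exposure is defined.
- *The programme is revised every year, so growth is certain.* The dissemination plan describes biannual forums, with the intervention changed only if needed.
- *The primary mortality analysis has the same fault.* Mortality uses Cox regression. The Effectiveness section names intervention exposure as the explanatory variable and Table 4 names survey year; neither gives the coding or says that time and district terms are added.

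**Conclusion.** The point holds for the reach and adoption outcomes and should be acted on. As stated, the pre/post term is unbiased only if the measured effect is equal at one, two, three and four years of exposure. Otherwise growth is underestimated and fading is overestimated, with a size set by the unknown shape: from no bias (constant), through about a quarter lost (fast uptake), to an estimate of 5 to 8 points against a mean of 25 (linear rise, r of 0.4 or more; 15 at r = 0).

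The firmest part concerns prenatal care, place of birth and post-natal care. Their two-year recall alone reduces an immediate constant effect to about 0.50 to 0.57 of its size (0.70 at r = 0), with no assumption about programme growth beyond births being spread evenly over the window.

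The figures rest on a linear approximation, an assumed r, and an exposure schedule read from the text, since the timeline in Table 2 is not shown. No conclusion is drawn for mortality.

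**What to change.** For reach and adoption:

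- Replace the pre/post indicator by indicators for completed years since the district's rollout (1, 2, 3, 4), keeping the time and district terms.
- Report the unweighted mean effect over years 1 to 3 as the main estimate. Report year 4 descriptively: it comes from one district, and no district is unexposed at 48 months.
- Keep the single-term model as a secondary analysis.
- For the two-year-recall outcomes, also classify each birth or pregnancy by whether it fell before or after rollout. Without this step the year 1 to 3 mean would still show only (0.5 + 1 + 1) / 3 = 0.83 of an immediate constant effect.

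For mortality, state how intervention exposure is coded. The same coding by year is advisable only if exposure is a single indicator in a model that also has time and district terms.

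**Cost.** The exposure coding changes analysis wording only; classifying births and pregnancies needs their dates, which the birth history should supply for births. The standard error of the main estimate is about 1.2 to 1.4 times that of the single term, a real loss with four districts. Ending the average at year 3 is a judgement, and the protocol should state it before the data are analysed.

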### Study setting

The study will be conducted in the catchment areas of 21 public sector health facilities within the Kara region’s rural districts of Bassar, Binah, Dankpen, and Kéran. The total population is approximately 181,111 people. Study sites were selected by MoH partners and IH programmatic staff based on perceived population health needs, ongoing regional public-private program activities, and population size. All selected sites are primary healthcare facilities operated by the MoH [53] that serve rural populations. Estimated catchment population and utilization rates for these sites are listed by district in Table 3. As described in Table 2, the ICBHSS initiative will be sequentially implemented by district each year within these 21 preselected sites.

**Table 3 Tab3:** List of study sites (*N* = 21) with estimated baseline catchment population (*N* = 181,111) and facility utilization rates

District	Study site	Catchment population*	Facility utilization rate**
Bassar	Bangéli	16,169	42%
Bassar	Kabou-Sara	10,054	56%
Bassar	Koundoum	7,428	37%
Bassar	Manga	5,006	28%
Bassar	Sanda-Afohou	5,514	43%
Binah	Asseré	4,446	19%
Binah	Boufalé	4,212	48%
Binah	Kouyorira	4,364	26%
Binah	N’Djei	3,258	53%
Binah	Pessaré	8,002	26%
Binah	Sirka	5,980	51%
Binah	Solla	5,960	58%
Dankpen	Koutière	13,097	12%
Dankpen	Kpétab	8,208	22%
Dankpen	Naware	19,531	10%
Dankpen	Solidarité	8,157	24%
Kéran	Kokou-Temberma	8,722	Unknown
Kéran	Nadoba	16,593	Unknown
Kéran	Natiponi	7,636	Unknown
Kéran	Pangouda	10,735	Unknown
Kéran	Warengo	8,039	Unknown

*Data derived from 2016 Ministry of Health population estimates and 2018 Integrate Health baseline population-based sampling

**Data source is 2016 Ministry of Health district-level annual reports

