#### Randomization

The cluster order for implementation at each step will be determined randomly by an external technical advisor using a random number generator. Randomization will occur each year 8 months prior to the rollout of the intervention in the next cluster. This will enable blinding to the random order of clusters for IH and MoH staff 7involved in implementation while also allowing for an annual 8-month planning stage prior to start of the intervention. Each cluster represents a district, with a total of 21 preselected health facilities across each of the four districts.

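### The reach and adoption model, as naturally read, gives no variance to district-specific year-to-year change, so its test holds 5% only if that variation is zero

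*Protocol article*

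**What the plan says.** The Reach section states the model itself: a mixed-effects generalized linear model comparing proportions before and after the intervention, "while adjusting for clustering at the facility and district level and time and allowing for district-level estimates to be random effects". It adds: "Our primary analysis will not include adjustment for individual-level characteristics, as each district will serve as its own control". The Adoption section carries the model over, "applying the same approach described in the *reach* evaluation measures through mixed-effects generalized linear models", and Table 4 also names mixed-effects generalized linear models for the care cascades.

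The design section sets the layout: "It includes four clusters that organize intervention health facilities by district: Bassar, Binah, Dankpen, and Kéran". On the rollout: "The ICBHSS cluster initiation order will be randomized annually with four steps". The household surveys "will be conducted in each cluster at baseline, 12, 24, 36, and 48 months". The Randomization section confirms the unit: "Each cluster represents a district, with a total of 21 preselected health facilities across each of the four districts". New households are sampled each year.

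The article names no district-by-survey term, no between-year correlation and no small-sample reference distribution. The one ICC, 0.005, is in the sample size section and is for under-five mortality.

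**The concern.** Having each district as its own control removes only what is constant in that district. A common time effect removes only what all four districts share. What is left, one district's coverage moving in one year for reasons unrelated to the programme, is shared by all of that district's facilities and respondents. Because the whole district switches at once, that movement lies on the same contrast as the exposure term. A model with time-constant district and facility effects assigns it zero variance.

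Sampling more households does not average it out. It reduces only the sampling error, so the understatement of the standard error grows with the sample. Reach and adoption serve one of the two primary aims and are meant to inform national policy, so intervals that are too narrow matter.

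**Working it through.** **Plan's own figure.** There is none on this point. The article gives no power or type I error for reach or adoption; its 7600 participants and 80% power concern mortality.

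**Inputs from the article.** 4 districts; 5 surveys; 21 facilities (5, 7, 4 and 5 by district, counted from Table 3); 7600 participants; 20% non-response; 0.5 children under five per participant; ICC 0.005. The article does not say whether 7600 is the total or the number per survey, so both are shown.

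**Respondents per district-survey cell (n).**
- All participants: 7600 × 0.8 / 20 = 304 (total) or 7600 × 0.8 / 4 = 1520 (per survey).
- All children: × 0.5 = 152 or 760.
- Ill children, assuming 25% are ill: × 0.25 = 38 or 190.

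**Assumptions.** Between-year correlation within a district ρ = 0.8, varied below; ICC 0.005 borrowed from mortality, or 0.02 assumed for coverage.

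**Formula.** With coverage p, the district-survey variance is ICC(1 − ρ)p(1 − p), and the sampling variance of a cell is about p(1 − p)/n. Their ratio is r = n × ICC × (1 − ρ), in which p cancels. Constant district and facility effects drop out of the within-district contrast, so the true standard error is about √(1 + r) times the model's. A nominal 5% test then rejects with probability 2[1 − Φ(1.96/√(1 + r))].

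Example: n = 304 gives r = 304 × 0.005 × 0.2 = 0.304 and √1.304 = 1.142. Then 1.96/1.142 = 1.716, and the rejection rate is 8.6%.

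| ICC | n per cell | r | √(1 + r) | Formula | Simulation, about |
|---|---|---|---|---|---|
| 0.005 | 38 | 0.038 | 1.019 | 5.4% | 6% |
| 0.005 | 190 | 0.190 | 1.091 | 7.2% | 7% |
| 0.005 | 152 | 0.152 | 1.073 | 6.8% | 6-7% |
| 0.005 | 760 | 0.760 | 1.327 | 14.0% | 14% |
| 0.005 | 304 | 0.304 | 1.142 | 8.6% | 8-10% |
| 0.005 | 1520 | 1.520 | 1.587 | 21.7% | 22% |
| 0.02 | 38 | 0.152 | 1.073 | 6.8% | 7% |
| 0.02 | 190 | 0.760 | 1.327 | 14.0% | 13% |
| 0.02 | 304 | 1.216 | 1.489 | 18.8% | 20% |
| 0.02 | 1520 | 6.080 | 2.661 | 46.1% | 45% |

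The simulation used the actual layout with random rollout order, 40% coverage, an assumed facility ICC of 0.02 and 2000 trials per setting. It gave the planned model its true facility and district variances, which favours the plan. Single runs scatter by 1-2 points.

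**Sensitivity to ρ, ICC 0.005, n = 304 / 1520.** By the formula, ρ = 0.9 gives r = 0.152 / 0.76 and rejection 6.8% / 14.0%; ρ = 0.5 gives r = 0.76 / 3.8 and 14.0% / 37.1%. At ρ = 1, r = 0 and the test is nominal.

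**Other model readings.** With variance components estimated and coverage 30%, a separate simulation gave 11-12% / 21-24% at ρ = 0.8. Reading the random district estimates as random district intervention effects gave 8% / 16%.

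**The alternatives.** Ordinary least squares on the 20 cell means with district and survey effects has 20 − 4 − 4 − 1 = 11 residual degrees of freedom (critical value 2.20). It rejected about 4-6% of the time in every setting. The mixed model with a district-by-survey term gave 2-6% against t with 11 df and 4-9% with a Wald z test (ICC 0.005).

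**The case against.** **The wording is one loose sentence of an article.** Time could be meant as a clustering level, the random district estimates could be intervention effects, and a full list of random terms is normal SAP content. This has some force: nothing in the article rules out a district-by-survey term. But the article does name its variance structure, and on the natural reading that structure omits the term that matters. The intervention-effect reading reduces the inflation without removing it.

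**The large figures fit few indicators.** This stands. Of the 11 reach indicators in Table 4, four concern children and four concern recently pregnant or post-partum women, so their denominators are well below 304 or 1520. Two of the remaining three count visits or treatment by the programme's own community health workers, for which a null with substantial pre-rollout coverage is of no interest. Only facility treatment matches the all-participant setting.

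**Stronger readings that the documents do not support.** A reader might infer that the test always rejects too often; it does so only if district-by-year variance is above zero, and no value is given. A reader might infer that an ineffective programme would be declared effective on several indicators; no calculation across indicators shows that. A reader might take the site-selection factors, "perceived population health needs, ongoing regional public-private program activities, and population size", as evidence of district-year shocks; they are only selection criteria. The Discussion does concede temporal trends and contextual factors as limitations, but without their size.

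**Conclusion.** The concern holds in conditional form. With four randomised districts that switch whole, the stated reach and adoption test is valid only if districts do not depart from the common time path beyond sampling error.

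At ICC 0.005 and between-year correlation 0.8, both assumptions for coverage outcomes, type I error is about 8-10% at 304 respondents per cell and 22% at 1520. It is about 6-14% for an indicator covering all children (152-760 per cell), and close to nominal, about 6-7%, for ill-child indicators (38-190). With a coverage ICC of 0.02 these become about 7-13% at 38-190 per cell and 20-45% at 304-1520.

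The affected indicators are facility treatment, antenatal care, facility birth, post-natal care, prompt treatment and care-seeking. The primary mortality outcome has a different analysis, Cox regression, and is not covered by this point. The change should be made because the replacement is valid whether or not the variation is present, while the stated test is valid only when it is absent.

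**What to change.** In the Reach section, keep survey as a fixed factor, add a district-by-survey random effect to the facility and district terms, and test exposure against a t distribution with 11 degrees of freedom. The t reference should be written in, because the Wald z version still reached 9%. Alternatively, specify an analysis of the 20 district-survey means with district and survey effects and t on 11 df; this is simpler and held its level in every setting simulated. Carry the change to Adoption by reference. In Table 4, point the care-cascade entries to the Reach model; they now point to the primary effectiveness outcome, whose stated analysis is Cox regression.

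No new data are needed. The cost is wider intervals and less power for reach and adoption. The t reference alone widens intervals by 2.20/1.96 = 1.12. At ICC 0.005 and correlation 0.8, the total factor is about 1.142 × 1.12 = 1.28 with 304 per cell and 1.587 × 1.12 = 1.78 with 1520.

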#### Community-based household surveys

Females 15–49 years of age who reside in a selected household within the study catchment area are included. Participants 15–17 years of age will only be included if they have been/are currently pregnant and have a waiver of parental permission. Households will be randomly selected each year using a systematic population-weighted sampling methodology. If there is more than one eligible respondent in the household, one will be randomly selected based on a Kish selection grid [54]. All participants will have the opportunity to decline participation during the informed consent process.

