#### Primary aim 1: effectiveness

##### Effectiveness

We define *effectiveness* metrics as those that assess the impact of the ICBHSS initiative using annual community household surveys, routine programmatic data, and the health facility assessments. The community-level primary outcome by district uses under-five mortality rates as well as the secondary outcomes of neonatal, under-one, under-two, and maternal mortality rates. We will additionally evaluate quality of care parameters focusing on timeliness of child healthcare through promptitude of treatment reception following illness diagnosis and health facility readiness scores. Lastly, we will assess equity through secondary analyses of under-five mortality by household wealth quintiles, maternal education levels, and distance from the nearest health facility.

*Primary outcome: under-five mortality rates*. We will calculate under-five mortality rates from all births reported by respondents using a standard birth/death history table. We will calculate under-five mortality rates and compare the risk of death before age five across surveys with the Cox proportional hazards regression using intervention exposure as the explanatory variable. Children still alive and under age five at the time of survey will be right censored.

*Secondary outcomes: neonatal, under-one, and under-two mortality rates*. We will calculate the neonatal, under-one, and under-two mortality rates from all births reported by respondents using the same methods described above adjusted for 28 days, 1 year, and 2 years.

*Secondary outcome: maternal mortality*. We will calculate an exploratory maternal mortality analysis based on sisterhood reports [57, 58].

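### Reach and adoption models leave out individual covariates because each district is its own control, but every survey draws new households, so the reason fails and a small, nearly free gain in precision is forgone

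*Protocol article*

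**What the plan says.** The Reach section of the protocol article plans a mixed-effects generalised linear model comparing proportions before and after the intervention, "adjusting for clustering at the facility and district level and time and allowing for district-level estimates to be random effects". It then fixes the covariate rule: "Our primary analysis will not include adjustment for individual-level characteristics, as each district will serve as its own control". The Adoption section takes over the same model, "applying the same approach described in the *reach* evaluation measures through mixed-effects generalized linear models".

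The inclusion criteria for the household survey describe the sampling: "Households will be randomly selected each year using a systematic population-weighted sampling methodology". Where a household has several eligible women, "one will be randomly selected based on a Kish selection grid".

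On the design: "It includes four clusters that organize intervention health facilities by district: Bassar, Binah, Dankpen, and Kéran". Surveys "will be conducted in each cluster at baseline, 12, 24, 36, and 48 months".

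The Effectiveness section plans equity analyses of under-five mortality by "household wealth quintiles, maternal education levels, and distance from the nearest health facility", so these characteristics will be recorded.

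**The concern.** The covariate rule is a stated decision with a stated reason, so it can be judged without the analysis plan. The reason would be sound if the same people were followed over time, or if nothing about the respondents varied between rounds. Neither is the case: the women interviewed after rollout are a different sample from those interviewed before.

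Two things are at stake for coverage and care-seeking. First, chance differences in respondent mix between district-surveys stay in the estimate, and there are only four districts, one per step, over which they can average out. Second, outcome variation that age, education and distance could explain stays in the residual. Neither threatens the validity of the unadjusted analysis. Both can be reduced with variables the survey needs anyway.

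**Working it through.** The article gives no precision figure for the reach or adoption measures. Its sample-size statement concerns under-five mortality and does not bear on this point, except as a source for cell sizes and the intracluster correlation (ICC).

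**Inputs from the article.** 4 districts, 5 surveys, ICC 0.005, 20% non-response, 7600 participants. The article does not say whether 7600 is a total or a number per survey, so both are shown. I take it as the number approached:
- total over all surveys: 7600 / (4 × 5) × 0.8 = 304 responders per district-survey
- per survey: 7600 / 4 × 0.8 = 1520 responders per district-survey

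**Assumptions.** Reach proportion 50%; share of outcome variance explained by covariates (R²) 2 to 20%; for step 2, a covariate held by 50% of women with a 20-point difference in outcome. The article gives none of these.

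**Step 1: what self-control removes.** Write the outcome for a woman in district i at survey j as time_j + θ·X_ij + district_i + β·x + error, where X_ij marks rollout and x is, say, schooling. Comparing a district with itself cancels district_i. It leaves β × (mean of x after − mean of x before), because the two samples contain different women. With random samples from an unchanged population, that term has expectation zero but not variance zero.

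**Step 2: size of that term within one district.** The SD of the difference in a 50% covariate between two independent samples is √(2 × 0.25 / m):
- m = 304: √(0.5 / 304) = 4.1 points; × 0.20 = 0.8 points in the outcome
- m = 1520: √(0.5 / 1520) = 1.8 points; × 0.20 = 0.4 points

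This assumes simple random sampling. It is sampling noise that the unadjusted standard error already contains.

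**Step 3: how one district-survey enters the effect.** I used a linear Hussey-Hughes model with time effects and a random district effect. The facility level is omitted for simplicity. V = (σ²/m)·I + τ²·J, with σ² = 0.995 × 0.25 and τ² = 0.005 × 0.25; D_i holds the time indicators and the rollout column for district i. Then Var(θ) is the last diagonal element of (Σ D_i′V⁻¹D_i)⁻¹. At m = 304 the weights over the five surveys in the first district to start are −0.164, 0.300, 0.145, −0.009 and −0.164. The largest absolute weight in any cell is 0.30, at both cell sizes. A 1-point change due to mix in a single cell therefore moves the effect by at most 0.30 points.

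Two further features matter. Within each survey the weights sum to zero across districts, so the estimate contrasts districts at the same time and the time effect absorbs any shift common to all. Within the first district they sum to about 0.11, not zero, so the model is not purely own-control.

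**Step 4: precision gain.** Replace σ² by σ²(1 − R²):

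| R² | SE, m = 304 (points) | ratio | SE, m = 1520 (points) | ratio |
|---|---|---|---|---|
| 0 | 2.25 | 1 | 1.04 | 1 |
| 2% | 2.23 | 0.991 | 1.03 | 0.990 |
| 5% | 2.20 | 0.976 | 1.01 | 0.975 |
| 10% | 2.14 | 0.952 | 0.98 | 0.949 |
| 20% | 2.03 | 0.900 | 0.93 | 0.896 |

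If district effects drift between surveys (assumed cluster autocorrelation 0.8), R² of 5% and 10% gives ratios of 0.982 and 0.964 at m = 304, and 0.990 and 0.981 at m = 1520.

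**The case against.** The strongest reply is that a prespecified unadjusted primary analysis, with randomly drawn households and a randomised rollout order, is legitimate. That stands. The rule is also limited to the primary analysis, so an adjusted secondary model is not excluded and may appear in documents not shown. The home-visit and home-treatment measures by programme community health workers should be near zero before rollout, so small shifts in mix hardly matter there. Facility clustering, already in the model, will take up part of what distance explains. With a logit link, adjustment would change the odds ratio from marginal to conditional, so adjustment is not neutral unless the effect is reported on a marginal scale.

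A reader might infer three stronger things that the article does not support:

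- **That shifts in sampling bias the effect.** Random redrawing from the same catchments gives noise. The article allows for 20% non-response, and the programme brings free care and home visits, so participation could change with rollout. That is a conceivable route, but nothing in the article shows it happening.
- **That a change of mix in one district-survey passes whole into the effect.** The weight of at most 0.30 rules this out.
- **That the primary outcome is affected.** Table 4 describes the adoption models as following the primary effectiveness outcome, which could suggest a shared rule. However, the Effectiveness section and the primary-outcome entry in Table 4 both specify Cox regression, and the covariate sentence stands only under Reach.

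None of this rescues the reason given. The objections bear on the size of the gain, not on whether self-control holds the sample's composition constant.

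**Conclusion.** The point holds as a cheap improvement with a modest benefit. The own-control reason does not justify leaving out individual covariates when each round interviews different women. What is forgone is some protection against chance imbalance across four districts and a small gain in precision. At an assumed R² of 5 to 10% the standard error would be about 2 to 5% lower, or about 1 to 4% lower if district effects vary between surveys as assumed above. At R² of 20% and stable district effects it would be about 10% lower.

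These figures rest on assumed covariate strength, a 50% proportion, a linear approximation without the facility level, and two readings of the 7600. The relative gain hardly depends on which reading is right when district effects are stable. The unadjusted analysis is not invalid, and the finding is confined to reach and adoption.

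**What to change.** In the Reach section, delete the statement that each district serving as its own control makes individual adjustment unnecessary. Prespecify that the reach and adoption models adjust for maternal age, maternal education, distance to the nearest facility and, for child outcomes, child age. Education and distance are already used in the equity analyses. Maternal age is needed for the 15 to 49 eligibility rule, and child age for the under-five measures and birth histories. The programme is unlikely to change any of the four. Leave wealth out, because removing charges at the point of care could affect household resources.

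Report standardised marginal differences in proportions so that adjusted and unadjusted results share one scale, and keep the unadjusted model as a sensitivity analysis. If the sponsor prefers the unadjusted model as primary, the minimum change is to correct the reason and prespecify the adjusted model as the sensitivity analysis.

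The cost is a change of analysis wording, with no new data collection. The downside is a few records with missing covariates, for which a handling rule should be stated.
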